### Study setting

The study will be carried out at Teaching Hospital, Peradeniya. Teaching Hospital Peradeniya is a large tertiary care teaching hospital in the Central Province of Sri Lanka. Most patients who attempt self-poisoning in the Central Province and surrounding regions, and who require medical care, are admitted for medical management to the Toxicology Unit (Ward 17) of this hospital [34].

### Phase 1—Randomized controlled trial

#### Inclusion criteria

Persons aged 16 years and over admitted to the study hospital for medical management of non-fatal self-poisoning during the study period, will be considered eligible for the participation in the study. Persons with first, as well as repeat, attempts of self-poisoning will be considered eligible for inclusion in the study. Further, we will be including bilingual persons who are fluent in speaking in Sinhala as well.

#### Exclusion criteria

Persons who state or carry reports indicating a previous diagnosis of mental retardation or dementia, and those who are physically too unwell to participate in the interview, will be excluded. Those who are not fluent in spoken Sinhalese will also be excluded from the study.

Potential participants will be provided verbal and written information about the study, and those who give written informed consent will be recruited to the study. The principal investigator will talk to potential participants and obtain informed consent.

### Enrollment and randomization

Participants who meet the inclusion criteria as described above, who have given written informed consent, will be randomly allocated (concealed) to either the intervention arm or the control arm. Those randomized to the intervention arm will receive the intervention in the form of a counseling session by a trained nurse. Both the intervention and control groups will receive medical care and treatment as usual (TAU) during their hospital stay. This will include medical management as well as psychiatry input for all irrespective of the intervention/control status of the participant. Care will also be taken to ensure that the intervention does not interfere with any treatment as usual.

Recruitment and intervention will be conducted over a consecutive 5-month period, or until the required number of participants are enrolled, and the end date of the study will be 12 months after the baseline intervention.

#### Randomization procedure

The intervention will be assessed using block randomization technique, in order to reduce bias and achieve balance in the allocation of participants to the intervention and control arm. An allocation sequence will be provided by the off-site statistician (independent of the research team) and will be based on a computer-generated list of random numbers, to allocate patients to the intervention plus TAU or TAU alone.

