### Outcome measures

#### Baseline assessment

Qualitative interviews will be conducted with participants, as described in the “Phase 2—Qualitative study” section below. The following assessments will also be completed among all participants: assessment of level of suicidal intent associated with the recent act of non-fatal self-poisoning (via the Pierce Suicide Intent Scale (PSIS), an internationally used scale for the assessment of suicide intent that has been used previously in Sri Lanka [35]) and presence of depression (via the Patient Health Questionaire-9 (PHQ-9) [36, 37] and Peradeniya Depression Scale (PDS) [38]). The PHQ-9 is a well-recognized tool for the screening of depression and has been validated for use in Sri Lanka, with the cutoff score of 10 or above indicating the presence of depression [38]. The PHQ-9 can also be used to examine the severity of depressive symptoms, with scores of 1–4, 5–9, 10–14, 15–19, and 20–27, indicating minimal, mild, moderate, moderately severe, and severe depressive symptoms, respectively [38]). The PDS is a screening tool for the identification of depression that was developed and validated for use in Sri Lanka, which considers the local cultural idioms of distress [38]. Participants will also be screened for anxiety (via the Generalized Anxiety Disorder 7-item scale (GAD 7)) [39] and psychological distress (via the General Health Questionnaire (GHQ 30)) [40] and assessed for coping strategies (via the Brief Coping Inventory, Brief COPE [41]). As far as possible, scales that have been translated to the local language and validated for use in Sri Lanka will be used. In the case of the GAD 7 and the Brief COPE, no validated versions are available, but these scales will be translated to Sinhala and back-translated and checked for accuracy prior to use. The baseline investigations will be carried out a few days (up to a week) after the act, allowing time for recovery from the immediate distress following the act of non-fatal self-poisoning.

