#### Sample size

Previous interventional studies have examined for changes in the severity of depression, using the PHQ-9 as an outcome measure [42]. One study reported that patients in the intervention group had significantly fewer depressive symptoms compared with patients in the usual care group at 12 weeks follow-up, and the PHQ-9 mean score at 3 months follow-up was 2.4 and 7.1 in the intervention and control group respectively (4.7 mean difference) [42]. The difference between the groups was significant (*p* < .001) using baseline scores as the covariate. A sample size of 15 in each group gave an 80% power to detect the difference in means of 4.7, assuming that the estimated common standard deviation is 4.49 and using a two-group *t* test with a two-sided significance level of 0.05 [42]. Based on similar calculations and allowing for a 50% drop-out rate, we calculated a minimum of 30 participants in each group; however, since our study will be conducted among those who have attempted self-poisoning, we anticipate (based on previous studies) that a little less than 50% of the sample will be suffering from depression [43]. Furthermore, through this intervention, we are planning to examine for clinically relevant changes of depression levels (PHQ-9 scores above 10, indicating a moderate level of depression or above, rather than in the < 10 range quoted in the previous study). To allow for this greater margin, we plan to recruit a sample of 150 intervention and controls.

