### Analysis

A strict intention to treat approach will be followed in the analysis. For missing data with regard to the main outcome, variable imputation will be used. The study and the control groups will be described using descriptive summary statistics (mean, standard deviation, count percent). The effect of the intervention will be assessed with a relative risk of severity of depression and other endpoints such as coping skills, levels of anxiety, depression, alcohol misuse, and repetition of self-harm.

Analyzing the qualitative interviews will be started parallel to the conducting of the interviews. The researcher will read the interview transcripts carefully several times to have a sense of the whole data, identifying emerging themes and categories [45]. She will discuss emerging themes, concepts, and contradictions with other designated investigators in the study. A code book will be created and modified until the final set of codes is obtained and reached to the data saturation point when there is no emergence of further new themes.

Qualitative data analysis will be conducted using a thematic content analysis approach following a systematic process. Codes will be applied to the transcripts and converted into categories to represent the main themes arising from the data [46]. Triangulation of themes and concepts will be used to further compare and contrast the data from the different participating groups. It is anticipated that this will strengthen the reliability and validity of the analysis. The analysis will be conducted in the original Sinhala language, and final themes will be translated into the English language by the researcher in cooperation with a professional translator.

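### The efficacy comparison is described as a relative risk with no baseline term, although the baseline scales are collected on everyone; adjusting for them is a low-cost gain in precision and protection against chance imbalance

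*Protocol article*

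**What the plan says.** All places are in the protocol article.

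- **Randomization procedure.** Allocation uses blocks: "The intervention will be assessed using block randomization technique, in order to reduce bias and achieve balance in the allocation of participants". An independent off-site statistician supplies the sequence, which "will be based on a computer-generated list of random numbers, to allocate patients to the intervention plus TAU or TAU alone". No stratification factor is named.
- **Analysis.** "The effect of the intervention will be assessed with a relative risk of severity of depression and other endpoints". The section adds intention to treat, imputation for the main outcome and descriptive summaries of both groups. It names no covariate.
- **Baseline assessment.** PHQ-9, GAD 7, GHQ 30 and Brief COPE are completed by all participants. PHQ-9 is read "with the cutoff score of 10 or above indicating the presence of depression". The follow-up section reassesses depression, anxiety and coping at 6 months and 1 year with the baseline measures.
- **Sample size.** The authors expect that "a little less than 50% of the sample will be suffering from depression" and use this as one reason to recruit more than the calculated 30 per group. They report that the cited study's group difference was obtained "using baseline scores as the covariate".
- **Inclusion criteria.** "Persons with first, as well as repeat, attempts of self-poisoning will be considered eligible for inclusion in the study". Repetition is a secondary outcome at both follow-up visits.

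**The concern.** Blocks keep the arm counts level but do nothing for case mix. Here the baseline state of the main efficacy measure is expected to divide the sample nearly in half, and baseline depression is likely to predict depression at 6 and 12 months. If the arms differ by chance in the share depressed at the start, a crude relative risk carries that difference into the estimate.

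The information needed to deal with this is already collected. The article relies on a precedent that used it, but describes its own effect estimate without it. What is at stake is the precision and interpretability of the exploratory efficacy estimates. Under Background the pilot is also meant to inform the sample size of a later trial, so a noisier estimate carries forward.

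**Working it through.** **1. The plan's own figure.** Inputs from Sample size: difference 4.7, SD 4.49, two-sided 0.05, 80% power.

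n per group = 2 × (1.960 + 0.842)² × (4.49 / 4.7)² = 14.3, rounded up to 15. With 50% drop-out, 15 / 0.5 = 30.

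Both stated figures reproduce (the exact t test gives 79.0% power at 15). Neither is wrong because of the present point. The calculation is an unadjusted two-group t test.

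**2. Chance imbalance in baseline depression.** Inputs: share depressed 0.48, assumed as a reading of a little under half; 1:1 allocation, assumed. The wording leaves open whether 150 is the total or the number per arm, so I use 75 and 150 per arm. I add 37 per arm, which is 75 after the plan's 50% drop-out.

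SD of the between-arm difference = √(2 × 0.48 × 0.52 / n), with a normal approximation for P(gap ≥ 10 points):

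| n per arm | SD (points) | 10 / SD | P(gap ≥ 10 points) |
|---|---|---|---|
| 37 | 11.6 | 0.86 | 39% |
| 75 | 8.2 | 1.23 | 22% |
| 150 | 5.8 | 1.73 | 8% |

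For repeat attempters, at an assumed 20% share, the SD at 75 per arm is √(2 × 0.2 × 0.8 / 75) = 6.5 points and the chance is 13%. At 150 per arm it is 3%.

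**3. What a 10-point gap does when there is no effect.** The article gives no follow-up risks, so three assumed pairs are used (risk if depressed at baseline / risk if not):

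- 0.50 / 0.12, share 0.48: (0.43 × 0.50 + 0.57 × 0.12) / (0.53 × 0.50 + 0.47 × 0.12) = 0.283 / 0.321 = 0.88, reciprocal 1.13.
- 0.60 / 0.20, share 0.50: 0.38 / 0.42 = 0.90, reciprocal 1.11.
- 0.50 / 0.30, share 0.50: 0.39 / 0.41 = 0.95, reciprocal 1.05.

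**4. Error rates.** Simulation of 20,000 null trials per size, with share 0.50 and risks 0.60 / 0.20. The unadjusted two-proportion test is compared with a Cochran-Mantel-Haenszel test stratified by baseline depression.

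| n per arm | Unadjusted, overall | Unadjusted, given gap ≥ 10 points | Stratified test, given gap ≥ 10 points |
|---|---|---|---|
| 37 | 4.8% | 6.8% | 5.1% |
| 75 | 5.4% | 9.4% | 5.2% |
| 150 | 5.0% | 10.6% | 4.8% |

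**5. Gain from adjustment.**

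For a binary depression outcome, the share of variance explained by baseline status is R² = p(1 − p)(a − b)² / [m(1 − m)], where a and b are the two risks and m is the overall risk. The gain in effective participants is 1 / (1 − R²) − 1.

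- 0.50 / 0.30: R² = 0.010 / 0.240 = 0.042, gain 4%.
- 0.60 / 0.20: R² = 0.040 / 0.240 = 0.167, gain 20%.
- 0.50 / 0.12: R² = 0.0360 / 0.2110 = 0.171, gain 21%.

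For a continuous score in a linear model, the variance factor is 1 − r². At r = 0.4 it is 0.84 (gain 19%) and at r = 0.6 it is 0.64 (gain 56%). Both correlations are assumed.

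**The case against.** The strongest reply is that the article is silent rather than wrong. It never says that the estimate will be unadjusted or that there is one unstratified list. Covariates are commonly left to an analysis plan, and strata to a full protocol; neither is shown. The remark about a baseline covariate describes the cited study and does not bind this one. That stands: the point cannot be put as an error or a contradiction. What remains is that the effect estimate as described can be improved with data already in hand.

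Four stronger readings are tempting but unsupported.

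- A reader might infer that chance imbalance lets the trial mimic or hide an effect. Randomization without strata is valid, and overall type I error stays near 5% (step 4). The shift is also small beside sampling error. At 30% risk and 75 per arm, SE(log RR) = √(2 × 0.7 / (75 × 0.3)) = 0.25, so a null 95% interval runs from about 0.61 to 1.63. A relative risk of 0.88 lies half a standard error from 1.
- A reader might infer that the plan itself divides the sample by first or repeat attempt. Inclusion criteria only makes both eligible and gives no share, subgroup or analysis use. The case for that covariate is only that it plausibly predicts repetition.
- A reader might conclude that allocation must be stratified. That is a debatable trade in a small pilot. With 150 in total and independent factors, the cell of depressed repeat attempters would hold about 0.2 × 0.48 × 150 = 14 people. Allocation would also wait for scales that may take up to a week after the act, when the session itself is due within a week and before discharge.
- The 19-56% gain should not be read onto the stated relative risk. It belongs to a continuous score.

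**Conclusion.** The point holds as a low-severity recommendation. As described, the effect estimate makes no use of baseline measurements that every participant provides. No stated figure is wrong because of this, and the unadjusted comparison is valid.

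The cost is lost precision, together with an error rate that rises from 5% to about 7-11% in those trials where the share depressed happens to differ by 10 points or more. Such a gap has a chance of 8% to 39%, depending on the number per arm analysed. The resulting shift in the relative risk, and the gain from adjusting, rest on assumed follow-up risks, correlations and a repeat-attempt share that the article does not give.

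Severity is low because feasibility and acceptability, assessed qualitatively, are the primary outcomes and efficacy is a secondary, exploratory aim.

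**What to change.** Add to Analysis that each treatment effect is estimated with adjustment for the baseline value of the same scale. For depression this means a relative risk adjusted for baseline PHQ-9, or a baseline-adjusted mean difference in PHQ-9 score. GAD 7, GHQ 30 and Brief COPE are handled in the same way where they are outcomes. Adjust the repetition comparison for first versus repeat attempt, and confirm that this status is recorded at baseline, since the article does not list it among the baseline assessments.

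The cost is a sentence or two in the analysis text and at most one baseline item. It needs no change to allocation or sample size, and it can be adopted after recruitment has begun, provided it is fixed before outcomes are compared by arm. Stratified block lists by baseline PHQ-9 (below 10, or 10 and above) are an option if the timing allows, but are not needed for this fix.

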#### Description and delivery of the trial intervention

The intervention consists of a brief single-structured counseling intervention delivered by trained nurses. It has been developed based on a similar intervention for self-harm described from Pakistan (C-MAPS) [26]. The C-MAP is a brief problem-focused therapy, conducted in six sessions over 3 months [26]. The aim of the original C-MAP intervention is to help the participant identify and resolve interpersonal difficulties, which cause or exacerbate distress. Previous work in Sri Lanka and South Asia have reported the common finding that self-harm is often associated with recent interpersonal conflict and associated with acute emotional distress (against a background of more complex factors), and the act is often carried out with a mixture of varied motives. Shortly after the act, the distress abates; but such persons have reported marked distress and mixed motivations at the time of the attempt—such as the desire to escape unbearable pain/thoughts/situation, inability to think of anything else to do, the wish to communicate, anger, shame, etc.

Therefore, in the current study, we have chosen to focus on the aspect of coping with the “acute emotional distress” associated with interpersonal conflict, and to do so, we have adapted the C-MAP therapy which has been developed and used in Pakistan [26]. This intervention focuses on acknowledging this distress and exploring alternate simple ways that suit participants to cope with such acute distress in the future. In this way, the nurses delivering the intervention will be encouraged and trained to, as far as possible, elicit ways of facing future crisis and negative emotions, from the person receiving the counseling himself/herself, and to then discuss and emphasis these strategies further.

The original C-MAP included sessions on introduction, dealing with crisis and problems, changing thoughts, and dealing with family problems. Some of these steps will be kept as the focus of this intervention as well—with a particular focus on dealing with crisis situations causing acute emotional distress [26]. But having multiple intervention sessions, which require the participants to return to the hospital after discharge, is unlikely to be practical in the context of this study—the participant attrition rate is likely to be high, and the demand on the nurses’ time, is also likely to be too much. And although the nurses will receive a training on delivering the counseling intervention, they will not have the expertise to deliver complex psychological therapies. Therefore, considering these factors, the intervention in this study will be limited to one session, delivered by nurses, prior to discharge from the hospital. Considering that the intervention is to be limited to one session and that the nurses do not have formal training in psychological therapies, the “changing thoughts” part of the original C-MAP therapy will be omitted from this intervention. Thus, the intervention in this study focuses more on identification and acknowledgement of problems or difficulties and exploration of alternate ways to cope with such situations of acute emotional distress in the future; this would include discussion of strategies such as emotional ventilation, relaxation, distraction, or self-soothing—guided by participant preferences as well.

The intervention will be carried out as a single conversational session, between a trained nursing officer and the participant. Each session will last about 30 min. It will be carried out in a confidential setting during hospitalization, within 1 week of the self-harm attempt (after the acute phase of the hospitalization when the participant has received medical treatment and management of the poisoning and its physical manifestations, but prior to discharge). At the end of the discussion, the participant will be given a brief, “take-home message’,” written in the form of a personalized note on the back of a pocket calendar, which sums up the main conclusions discussed by the nurse and the participant. The participant will be encouraged to keep the pocket calendar and message as a reminder of alternate ways of coping with distress; care will be taken, however, to write the message in a de-identified form, without any direct reference to the incident of self-poisoning, and without revealing any confidential information.

At the start of the RCT, the nurses delivering the intervention will receive a specific training, coordinated by the researcher, regarding the nature of the intervention as described above. This training will be conducted in the form of interactive workshops, conducted by the investigators, and will include demonstrations and role play. The training will include a basic introduction into what is meant by counseling, followed by training about the specific counseling required in this study. This will include aspects such as introduction, building up a rapport, listening to the participant, reflecting back, helping the person himself/herself identify the problem or trigger that led up to the act of self-poisoning, acknowledgment of the associated emotional distress, and exploration of alternate ways to deal with situations of acute emotional distress should it occur again in future. The need for maintenance of privacy and confidentiality will be stressed. There will be also a focus and discussion on limits and boundaries and identification of risks, as well as when and how to refer for further help. The training will include workshops and role play, and nurses will also be given a structured manual which outlines the principles of the counseling intervention, and they will be encouraged to use this as a guide when delivering the intervention.

During the nurses training, all attempts will be made to build confidence and provide a positive background towards carrying out this role in the ward. Possible challenges the nurses may face, such as time constraints, and other issues will be looked for and discussed during these workshops. Nurses will be encouraged to carry out the counseling at a convenient time. It will also be made very clear that the nurse’s participation and contribution towards this intervention are entirely voluntary. The nurses will also be given a structured manual which outlines the principles of the counseling intervention, and they will be encouraged to use this as a guide when delivering the intervention.

There will be an ongoing contact between the nurses involved in the study and the researcher to monitor for any difficulties during the implementation of the intervention. Before starting the intervention, the investigators will provide a description about the background and rationale of doing this study to other health staff who will be working at the study site to enlist their support.

All participants (intervention and control group) will receive medical care and treatment as usual during their hospital stay. This will include medical management as well as psychiatry referral, as deemed required by the medical team (which is the usual practice) irrespective of the case/control status of the participant. Care will also be taken to ensure that the intervention does not interfere with any treatment as usual.

